	2c: Sustainability: Sustained or renewed changes to staff work attitudes and outcomes related to work performance	TREC HCA Survey [36]	While quantitative data will be collected and analyzed over the course of the project, SSaSSy likely will not be adequately powered for statistical inference. Descriptive statistics including statistics of central tendency, dispersion, and standard deviation will be computed for each unit-level variable, for each booster arm collected through the TREC Survey waves. However, if changes in the primary outcome of the SCOPE intervention, Care Aide-reported *conceptual use of best practices*, are sufficient over the booster interval (e.g., an effect size of 0.29), we will use one-way ANOVA (repeated measures, within-between interaction) to test for “pre–post” differences in the means of each variable within and between groups/booster arms, followed by Tukey–Kramer test for significant differences between all pairs of groups if appropriate (where distributions are not normal the Kruskal–Wallis test will be used, and where data are heteroscedastic Welch's ANOVA will be used). In the more likely event that changes of this magnitude do not occur, we will compute p-values by time point before and after the SSaSSy booster interval. We are constrained in our sample size because we are studying the post-implementation of a trial with a fixed number of experimental sites.
(ii) SCOPE Templates refer to documents introduced during SCOPE implementation, in the all-team Learning Congresses, that are designed to assist care aide-led QI Teams in planning and managing their QI projects, and measuring and reporting their progress against their project aims			
(iii) The quality advisors keep diaries in which they prepared structured summaries of each interaction with the QI Teams, whether face-to-face or telephone, outside of the all-team Learning Congresses. Quality advisors also prepare written, structured, quarterly feedback reports for each QI Team			
	2e: Spread: Indications of spread to other units within the SCOPE intervention sites	Semi-structured in-person interview with the QI Team lead, senior sponsor, and QI advisor	As above

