Aim 3: Compare the effectiveness and costs of post-implementation support arms		Documentation of resources and associated costs for low- and high-booster conditions	This cost analysis is exploratory in nature. We plan a simple, disaggregated reporting of costs. We will report the intervention costs (costs to deliver the boosters) separately from the costs incurred by the participating units. Each unit will report their incurred costs for staff, training and materials and supplies. Disaggregated presentation will allow units to understand what is driving the costs and identify possible areas where costs could be modified within the overall intervention

### Phase 2

The second study phase will use a quasi-experimental design [37] to evaluate the relative effectiveness of the three post-implementation support conditions: two treatment groups (low-, and high-intensity post-implementation boosters) and an untreated control group (no booster). Pretest and post-test data [37] relating to sustainment and sustainability will be collected through TREC surveys and via unit-level RAI-MDS 2.0 quality indicators. Phase 2 will begin in June 2020 and involve trial sites in BC (17 units) and AB (14 units), where SCOPE implementation concluded in May 2019. Specifically, the untreated control group (10 units) will receive no post-implementation support, one treatment group (10 units) will be provided with a low-intensity booster, and the second treatment group (11 units) will receive a high-intensity booster.

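### The fallback the authors expect to use, p-values by time point, does not give a baseline-adjusted comparison of the booster arms

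*Protocol article*

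**What the plan says.** The aim 2c row of Table 1 covers the staff outcomes from the TREC survey. It warns that the study is unlikely to have adequate power for inference, plans descriptive statistics by arm, and then sets out two inferential branches.

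- **If changes in the SCOPE primary outcome are large enough** (an effect size of 0.29 is the example), the test is a "one-way ANOVA (repeated measures, within-between interaction) to test for “pre–post” differences in the means of each variable within and between groups/booster arms". Within this branch, "where distributions are not normal the Kruskal–Wallis test will be used, and where data are heteroscedastic Welch's ANOVA will be used".
- **If they are not**, which the authors consider more likely, "we will compute p-values by time point before and after the SSaSSy booster interval".

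The Phase 2 section says that pretest and post-test data "will be collected through TREC surveys and via unit-level RAI-MDS 2.0 quality indicators". It fixes the arms at 10 control, 10 low-intensity and 11 high-intensity units. The section on assignment describes random allocation to the three arms among units with high and with low levels of sustained activity. The strengths and limitations section counts the pretest and post-test measures as a strength of the design. It also says that the study must rely on descriptive statistics to judge relative effectiveness.

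**The concern.** Aim 2 and the Phase 2 section ask how the three conditions compare. The branch expected to apply yields p-values attached to time points, not an estimate of the difference between arms that uses both measurements.

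Two things are at stake. The first is interpretation: p-values set side by side invite a conclusion of the form *significant after but not before*, or *significant in one arm but not in another*, and neither is a test of a booster effect. The second is precision: the number of units is fixed by the parent trial, so the pretest is one of the few means left of narrowing the intervals, and this branch does not use it for that purpose.

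**Working it through.** The article gives no power, significance level, standard deviation or pre-post correlation for this comparison, so there is no stated figure to reproduce.

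**Step 1: the two readings of the sentence.**

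| Reading | What is tested | Relative booster effect, baseline-adjusted? |
|---|---|---|
| Arms compared at each time | Pretest: a null that random assignment makes true. Post-test: arm difference in level, pretest unused | No |
| Pre versus post within each arm | Change in each arm separately | No, the arms are not compared |

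**Step 2: separate tests are not a test of differential change.** Simulation with normal unit means, arms of 10, 10 and 11, and 6,000 runs. The arms were given a stable difference of 0.5 SD per step at both times and no differential change, at correlations of 0.5 and 0.7. The pretest comparison was significant in 47–48% of runs and so was the post-test comparison. The test on change rejected in 5%. Random assignment would produce such a difference only by chance; the run shows only that the tests answer different questions.

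**Step 3: the precision left unused.** From the article: 10 control and 11 high-intensity units, 31 in all. Assumed: pre-post correlation rho of unit means 0.3, 0.5 or 0.7; two-sided 5% level; equal variances; no multiplicity adjustment; SD is that of post-test unit means.

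- Variance factor v: post-only 1; ANCOVA 1 − rho².
- SE = SD × √[v(1/10 + 1/11)] = 0.437 × √v SD.
- Residual df = 31 − 3 = 28, so t(0.975) = 2.048. Half-width = 2.048 × 0.437 × √v = 0.895 × √v SD.
- Power from the noncentral t with noncentrality D/SE, for assumed true differences D of 1 SD and 0.5 SD.

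| Analysis | v | Half-width (SD) | Power, D = 1 SD | Power, D = 0.5 SD |
|---|---|---|---|---|
| Post-only | 1.00 | 0.90 | 60% | 20% |
| ANCOVA, rho 0.3 | 0.91 | 0.85 | 64% | 21% |
| ANCOVA, rho 0.5 | 0.75 | 0.78 | 72% | 25% |
| ANCOVA, rho 0.7 | 0.51 | 0.64 | 87% | 34% |

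The table keeps 28 df throughout. Taking off two, for the pretest and the sustained-activity level, lowers power by less than 0.003.

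**Step 4: the change score.** Its variance factor is 2(1 − rho): 1.40, 1.00 and 0.60 at rho 0.3, 0.5 and 0.7. A post-only comparison is therefore more precise than a change analysis below rho 0.5 and less precise above it. ANCOVA is at least as good as either at each value.

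**Step 5: Kruskal–Wallis and Welch.** With two time points, the within-between interaction F equals the one-way F on change scores (4.364 by both routes in a test data set). Either substitute, run on change scores, keeps the pretest and compares pre-post change between arms.

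**The case against.** A reader might infer that every fallback in the row discards the pretest. The text does not support that. Kruskal–Wallis and Welch are named as substitutes inside a test of pre-post differences, nothing says they use post-test scores only, and on change scores they keep the pretest. What remains is that their input variable is not named, which is worth a clause.

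Two further criticisms are tempting and also fail. The text never says that Tukey–Kramer follows Welch's ANOVA. The term one-way is qualified in the same parenthesis as a repeated-measures, within-between analysis.

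Nor is a post-only comparison invalid. Arms are randomly assigned, and its simulated type I error was 0.04–0.05. The faults are lost precision and no test of change, not false positives.

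The strongest objection is about weight. The authors say that power is inadequate and that they will rely on description, within one sub-aim of a mixed-methods study. The 1 SD effect is not in the article, and the fallback applies only when changes are small. At 0.5 SD, power is 34% at best in the table above, and at rho 0.3 the gain is slight. All of this stands and lowers the severity. It does not remove the point: the article still commits to p-values in this branch, and an estimate with an interval would serve a descriptive purpose better.

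**Conclusion.** The point holds for the by-time-point sentence. On either reading, the branch the authors expect to follow does not deliver a baseline-adjusted comparison of the arms, although the data for one will exist. This conclusion follows from the wording and needs no assumed figure.

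The size of the loss does rest on assumptions. If the sentence means post-only arm comparisons, intervals for high-intensity booster versus control are wider than necessary by a little at rho 0.3 (0.90 against 0.85 SD) and by much more at rho 0.7 (0.90 against 0.64 SD). The study stays underpowered for modest effects whichever analysis is used, as its authors say. Severity is moderate: the comparison is presented as mainly descriptive, and the planned interaction test in the other branch is sound.

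**What to change.** In the aim 2c row of Table 1, replace the by-time-point p-values with one ANCOVA per outcome: unit-level post-test on arm and pretest, plus the high or low sustained-activity level used in assignment. Report the three pairwise arm differences with 95% confidence intervals, label them exploratory, and drop the pretest p-values.

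If Kruskal–Wallis or Welch's ANOVA is kept in the other branch, state that it is run on pre-post change scores. The interaction test there need not be replaced.

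The cost is a few lines of wording, one regression per outcome and one or two degrees of freedom. No new data are needed.

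### In the branch the protocol expects to use, staff-outcome p-values are computed by time point with no stated contrast, and the comparison of change between arms is dropped

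*Protocol article*

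**What the plan says.** The Phase 2 section sets out to "evaluate the relative effectiveness of the three post-implementation support conditions", with 10 control units, 10 low-intensity units and 11 high-intensity units. Units are assigned at random within groups of high and low sustained activity.

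For staff attitudes and work outcomes, the Analysis column of Table 1 (Aim 2c) first states that "SSaSSy likely will not be adequately powered for statistical inference" and plans descriptive statistics that "will be computed for each unit-level variable, for each booster arm collected through the TREC Survey waves". It then sets two branches, chosen by the change seen in one outcome, Care Aide-reported conceptual use of best practices:

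- If changes "are sufficient over the booster interval (e.g., an effect size of 0.29"), then "we will use one-way ANOVA (repeated measures, within-between interaction) to test for" pre-post differences in each variable, "followed by Tukey–Kramer test for significant differences between all pairs of groups if appropriate".
- Otherwise, which the protocol calls more likely: "we will compute p-values by time point before and after the SSaSSy booster interval".

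The Strengths and limitations section adds that relative effectiveness has to be examined with descriptive statistics.

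**The concern.** Aim 2 compares the boosters with no booster, which the protocol equates with natural decay. The only analyses that it names for comparing arms, or change between arms, sit in the branch it does not expect to use. In the expected branch the whole inferential plan is one clause, and that clause names no contrast.

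Two readings are open, and they fail in different ways. Comparing arms at each time point leaves the collected pretest out of the effect estimate and adds a baseline test that says nothing about boosters. Comparing before with after inside each arm tests that arm against its own past. Decay, or any other change common to all 31 units, then feeds every p-value, although the untreated control is there to remove it.

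**Working it through.** **Inputs.** From the protocol: arms of 10, 10 and 11 units, unit-level variables, and one pretest and one post-test. Assumed, because the protocol gives none: two-sided alpha 0.05, unit-level SD 1, pre-post correlation ρ of 0.3 to 0.7, and the sizes of shift and effect below. The plan states no power or sample-size figure for this outcome, so there is none to reproduce.

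**Reading 1: arms compared at each time point.**

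1. Before the interval, randomly assigned arms differ only by chance, so the test is significant 5% of the time by construction.
2. After the interval, a shift common to all arms cancels. With no booster effect and a 0.5 SD shared shift, the simulated three-arm post-test was significant in 4.6% / 5.5% / 5.2% of trials at ρ = 0.3 / 0.5 / 0.7. The test is valid.
3. For power, take true means of 0, 0.5 and 1.0 SD. The weighted mean is (10×0 + 10×0.5 + 11×1.0)/31 = 0.516. The noncentrality is λ = 10(0.516)² + 10(0.016)² + 11(0.484)² = 5.24. With 2 and 28 degrees of freedom, power is 48% at any ρ.
4. Pretest adjustment divides the residual variance by 1/(1 − ρ²), so λ becomes 5.24/0.91 = 5.76, 5.24/0.75 = 6.99 and 5.24/0.51 = 10.28. Simulated power is about 51% / 60% / 76% at ρ = 0.3 / 0.5 / 0.7. The gain in information is 1/(1 − ρ²) = 1.10 / 1.33 / 1.96, whatever the effect size.
5. A plain comparison of change scores has λ = 5.24/[2(1 − ρ)] = 3.74 / 5.24 / 8.74 and power of 36% / 48% / 71%. Moving the interaction test into this branch would therefore lose power against the post-only test when ρ is below 0.5. Pretest adjustment does not have that weakness.

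**Reading 2: before against after within each arm, with no booster effect.** Let every unit shift by s. The paired difference has SD √[2(1 − ρ)], and the paired t-test has noncentrality s√n/√[2(1 − ρ)]. Let a be the chance that a 10-unit arm is significant, and b the same for the 11-unit arm. The arms are independent, so

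P(at least one booster arm significant, control not) = (1 − a)[1 − (1 − a)(1 − b)].

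Example with ρ = 0.5 and s = 0.5: the noncentralities are 1.58 and 1.66, giving a = 0.293 and b = 0.323. Then 0.707 × [1 − 0.707 × 0.677] = 0.37.

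| Shared shift (SD) | ρ = 0.3 | ρ = 0.5 | ρ = 0.7 |
|---|---|---|---|
| 0 | 9% | 9% | 9% |
| 0.29 | 19% | 22% | 29% |
| 0.5 | 32% | 37% | 40% |
| 0.8 | 39% | 34% | 17% |

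The rate falls at large shifts because the control arm then becomes significant too. Simulations of the same settings gave 17% to 29% at 0.29 SD and 33% to 39% at 0.5 SD, within two percentage points of the formula. In the 0.5 SD setting, a test of change by arm stayed at 4.7% to 5.0%.

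**The case against.** A reader might infer that no p-value in this branch tests a booster against no booster. The document does not support that. The phrase 'by time point' fits a comparison of arms at each time point at least as well as a before-after test. Under the random assignment described, the post-interval comparison is then a valid test in which shared change cancels. The cost is efficiency, and an unadjusted randomised comparison is not an error.

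A reader might also infer that the authors will treat a significant booster arm beside a non-significant control as an effect. Nothing in the protocol says so. It plans descriptive statistics by arm, rests relative effectiveness on them, and plans comparisons both within and between arms in its narrative integration.

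The sizes are also conditional. The fallback applies only when the change in conceptual use of best practices is small. If 0.29 is a standardised mean change (the metric is not stated), a 0.5 SD shift in that outcome would point to the other branch, so the 0.29 SD row is the more relevant one for it. The same caution applies to the 0/0.5/1.0 SD differences in the power figures. The other staff variables follow the branch set by this one outcome and may move more.

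Finally, an article may leave the naming of a contrast to a fuller plan. That carries some weight. But the article does more than stay silent: it commits to p-values by time point, and it keeps the comparison of change between arms for the branch it does not expect.

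**Conclusion.** The point holds in a limited form. In the expected branch, the protocol commits to p-values whose contrast is unnamed and drops the comparison of change between arms. Under the between-arm reading the harm is lost precision, small at a correlation of 0.3 and substantial at 0.7, plus an uninformative baseline test. Under the within-arm reading the harm is a misleading pattern in about one null trial in five to two in five for shared shifts of 0.29 to 0.5 SD. It is about 9% with no shift. Correlation, shift, effect sizes and alpha are all assumptions.

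The point is moderate, not critical. The sentence governs only the staff survey outcomes of Aim 2c, in a study that says it is not adequately powered for inference.

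**What to change.** In Table 1, Aim 2c, replace the p-values by time point with one analysis used whatever the size of the observed change:

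- For each staff variable, report the low-minus-none and high-minus-none differences in post-test unit means, adjusted for the unit's pretest and sustained-activity group, with 95% intervals.
- Label these estimates exploratory, in line with the Strengths and limitations section.
- Show pretest means by arm as description, without p-values.
- Do not use within-arm before-after p-values as evidence about the boosters.

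The cost is a sentence or two in Table 1 and in the analysis plan. No new data are needed: the pretest is already collected, and the activity groups are already defined for assignment. The change resolves the ambiguity under either reading.

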#### Assignment to treatment and control groups

We plan to use a cut-off-based random assignment strategy [37]. First, the extent to which SCOPE-conveyed practices have been sustained just prior to SSaSSy start-up in BC and AB, nursing homes will be assessed through “baseline interviews” with the team and senior sponsors. This will be followed by random assignment of those with high levels of sustained activity, and those with low levels, to each of the low-intensity booster, high-intensity booster, and untreated control groups. This approach will be piloted in phase 1 amongst participating units in MB nursing homes.

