#### SSaSSy booster pilot

The low- and high-intensity boosters will be piloted in up to 7 units in 7 MB homes (potentially 3 low-intensity booster units, 4 high-intensity booster units) for 7 months, starting June 2019. The pilot interval will be followed by data analysis and refinement of boosters where we will focus on: (i) assessing relationships between the boosters’ contents and sustainment, sustainability, and spread; (ii) the clarity of the booster content from the perspective of the QI Teams; and (iii) the adequacy of the modes of delivery. Quantitative and qualitative data will be collected during the pilot; see Table 1 for a summary of measures relevant to each study aim.

**Table 1 Tab1:** SSaSSy aims, measures and analyses

Aim		Data/measures	Analysis
Aim 1. Explore site adaptation and/or contextualization		Semi-structured in-person interviews with the QI Team lead, senior sponsor, and QI advisor	A hybrid approach of qualitative methods will be used, thematic analysis [28], which incorporates both an inductive approach that allows themes to emerge from the data [29] and a deductive a priori template-of-codes approach [30] based on research we review above. Audiotapes of the interviews will be transcribed verbatim and data analysis will be completed using line-by-line coding and constant comparative methods [31]
Aim 2: Explore the relative effects of the high- and low-intensity boosters	2a: Sustainability: Sustained or renewed improvements to quality of resident care	Unit-level quality indicators generated using RAI-MDS 2.0 data on resident outcomes (mobility, pain, behavior)	Run charts will be generated for the RAI-MDS data^(i)^ collected SSaSSy start for each of the three quality indicators for each unit (RAI data elements MOB01/MOB1A; PAI0X/PAN01; BEHD4/BEHI4). For the clinical area on which QI Teams focus, we will analyze the relevant RAI-MDS quality indicator using statistical process control methods [32] and a procedure that members of our research team developed for the SCOPE proof of principle study [21] which categorizes control charts in terms of demonstrated changes to performance.
Notes:			

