#### Inclusion of non-equivalent dependent variables for each group

The quasi-experiment design will be further strengthened by including non-equivalent dependent variables, in addition to the target outcomes variables. We have a ready way in which to do this: each QI Team is instructed to focus on one of either resident mobility, pain management or reducing responsive behaviors, and we collect RAI-MDS 2.0 quality indicator data (see Table 1, aim 2a) on each of these clinical areas. For a QI Team focussing on mobility, for example, we consider the measure based on mobility indicators MOB01 and MOB1A to be our target outcome variable, while PAI0X/PAN01; and BEHD4/BEHI4 will serve as our non-equivalent dependent variables. That is, while in this example neither the pain nor behavior measures would be predicted to change because of the treatment (SSaSSy), they would be expected to respond similarly to contextually important internal validity threats in the same way as the mobility target outcome.

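### Phase 2 assignment balances only sustained activity, although the aim 2a resident indicator depends on each team's clinical focus; the arms' focus mix is left to chance

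*Protocol article*

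**What the plan says.** The section on assignment to treatment and control groups describes baseline interviews that grade how far SCOPE practices have been sustained, followed by "random assignment of those with high levels of sustained activity, and those with low levels" to the three conditions. It names no other balancing factor.

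The Phase 2 section gives 17 units in BC and 14 in AB, and arms of 10 (control), 10 (low intensity) and 11: "the second treatment group (11 units) will receive a high-intensity booster".

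On the resident outcome, the section on non-equivalent dependent variables says that "each QI Team is instructed to focus on one of either resident mobility, pain management or reducing responsive behaviors". For a mobility team, "we consider the measure based on mobility indicators MOB01 and MOB1A to be our target outcome variable". That team's pain and behaviour indicators are kept only as comparison series. Table 1, aim 2a, matches this: "For the clinical area on which QI Teams focus, we will analyze the relevant RAI-MDS quality indicator using statistical process control methods". The resulting charts are then sorted into categories of performance change.

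The limitations section says that the study is not powered for inference and that the arms will be compared with descriptive statistics.

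**The concern.** For aim 2a, units in the same arm can have different target outcomes. An arm's set of control-chart results is therefore a mixture of up to three indicators, and the stated assignment rule does not control the proportions. If one arm held mostly mobility units and another mostly behaviour units, a difference between them in chart categories could come from the booster, from the indicators, or from both. With 10 or 11 units per arm and a descriptive comparison, the two sources would be hard to separate afterwards. If an arm had no unit in one focus area, that area could not be compared for that arm at all.

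**Working it through.** **Inputs from the protocol article.** 31 units; arms 10/10/11; province 17/14; one balancing factor (high/low activity); one of three focus areas per team. The totals agree: 17 + 14 = 31 and 10 + 10 + 11 = 31. The article gives no sample-size derivation to reproduce.

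**Assumptions.** The number of units per focus area is not given, so three splits were tried: 11/10/10, 16/8/7 and 20/7/4. Activity level is taken as unrelated to focus and province; grouping by activity then leaves the chance distribution of focus unchanged.

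**Measure.** For each focus area, take each arm's share (count divided by arm size) and the largest share minus the smallest. The gap is the largest of these differences over the three areas. With 10 units in an arm, 30 points is three units (for example 5/10 − 2/10).

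**Result** (40,000 random 10/10/11 assignments per split):

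| Assumed focus split | Gap ≥ 20 points | Gap ≥ 30 points | Gap ≥ 40 points | Some arm has no unit in a focus area |
|---|---|---|---|---|
| 11/10/10 | 91% | 70% | 39% | 5% |
| 16/8/7 | 90% | 66% | 34% | 18% |
| 20/7/4 | 86% | 59% | 25% | 57% |

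The median gap is 30 to 32 points.

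**Province, for comparison.** With the stated 17/14 split, the gap is 30 points or more in about 45% of assignments and 40 points or more in 23%. By exact hypergeometric calculation, the two arms of 10 differ by three or more BC units in 27%.

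**What balancing would achieve.** The expected count in an arm is arm size × focus total / 31. For 11/10/10 in an arm of 10 this is 10 × 11/31 = 3.55 and 10 × 10/31 = 3.23; in the arm of 11 it is 11 × 11/31 = 3.90 and 11 × 10/31 = 3.55. Counts within one of these are 3 or 4 in every cell, so the largest possible gap is 4/10 − 3/11 = 12.7 points. The same steps for 16/8/7 allow 5 or 6 units of the largest area in every arm, and at most 6/10 − 5/11 = 14.5 points. For 20/7/4 the arms of 10 may hold 6 or 7 units of the largest area and the arm of 11 may hold 7 or 8, giving at most 8/11 − 6/10 = 12.7 points.

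**Whether enough assignments remain.** There are 31!/(10! 10! 11!) ≈ 1.6 × 10^13 assignments. Requiring focus, BC and high/low counts all within one of expectation, with an assumed 15/16 high/low split and the three factors mutually unrelated, leaves about 0.4% to 0.9%. Even 0.4% is 0.004 × 1.6 × 10^13 ≈ 6 × 10^10.

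**Why not simply add strata.** Activity × focus × province gives 2 × 3 × 2 = 12 strata of 31/12 ≈ 2.6 units, under one per arm. Activity × focus gives 6 strata of 31/6 ≈ 5.2 units, or 1.7 per arm.

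**The case against.** The case against has real force.

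- **The rule is valid as it stands.** Random assignment within activity levels has no expected bias, and almost any unbalanced factor would show similar gaps in 31 units. This stands, and it is why the point is an improvement and not an error. A journal article may also omit balancing factors that the full protocol holds, and the flow diagram is not shown; the point concerns the rule as stated.
- **There are safeguards.** Each unit is charted against its own history and placed in common change categories, the two other indicators serve as within-unit controls, and qualitative findings are integrated. A reader might infer that nothing later deals with the problem. That goes too far: these features soften it. None of them evens out the focus mix between arms.
- **Harm is not shown.** A reader might infer that an imbalanced mix would bias the comparison because one indicator is easier to move. The article says nothing about relative responsiveness, and it sets out no arm-level summary of chart categories. The simulation measures composition, not distortion.
- **Province is different.** A reader might infer that province also changes what is measured. It does not; it changes the setting. A 30-point gap in province is also less likely than not.
- **Focus may not be fixed.** A reader might assume that each team's focus is known and stable at assignment. Phase 2 starts about a year after SCOPE ended, and the article does not say whether teams keep their focus.

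**Conclusion.** The point holds for aim 2a and clinical focus. The stated assignment rule leaves the distribution of three different target indicators over three small arms to chance, and a gap of 30 points or more in some focus share is more likely than not (about 59% to 70%) under each split tried. This rests on the assumed splits and on activity being unrelated to focus. The descriptive aim 2a comparison may therefore partly reflect focus mix; by how much cannot be said from the document.

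For the staff survey outcomes (aim 2c) the measure is the same in every unit, so chance prognostic imbalance is the only issue there. The same applies to province.

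**What to change.** Keep the high/low activity grouping. Record each team's focus at the end of SCOPE or at the baseline interview. List the 10/10/11 allocations that respect the high/low grouping and in which each arm's count per focus area is within one of its expected share, and draw one at random. Add BC/AB as a secondary, marginal constraint for prognostic balance only. Present the aim 2a control-chart categories by arm with each unit's focus area identified. Treat this as description only, because a focus-by-arm cell holds about 31/9 ≈ 3.4 units.

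The cost is a short program at the single assignment step, with no extra units and no data beyond each team's focus. The downsides are that assignment must wait until all baseline interviews are scored, that the set of allowed assignments is smaller (though still very large), and that a team may change focus during the booster period, which would undo some of the balance. The assignment approach is due to be piloted in phase 1, so the step can be tried there.

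### Units are randomised within high- and low-sustainment groups, but the named between-arm tests and summaries have no term for those groups

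*Protocol article*

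**What the plan says.** Protocol article, Phase 2, Assignment to treatment and control groups: "We plan to use a cut-off-based random assignment strategy". Baseline interviews grade how far SCOPE practices have been sustained, and the plan is then "random assignment of those with high levels of sustained activity, and those with low levels, to each of the low-intensity booster" condition, the high-intensity condition and control. The section gives no cut-off, stratum sizes or blocking within stratum.

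Protocol article, Phase 2: there are 31 units in three arms, with 10 as controls, 10 in the low-intensity arm and 11 in the high-intensity arm.

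Protocol article, Table 1, aim 2c (staff survey variables): if changes are large enough (0.29 is the example given), a repeated-measures ANOVA with a within-between interaction tests for pre-post "differences in the means of each variable within and between groups/booster arms". Tukey-Kramer follows, with Kruskal-Wallis or Welch's ANOVA as alternatives. Otherwise, in the case called more likely, p-values are computed by time point. Descriptive statistics are given for each arm. None of these procedures mentions the high/low groups.

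The Strengths and limitations section counts the cut-off-based assignment as a strength of the design. It also says that the study will not be adequately powered and must rely on descriptive statistics.

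**The concern.** When units are randomised within groups formed on a baseline characteristic, the analysis should normally carry those groups. If it does not, and the arms are balanced within them, any between-group variation in the analysed variable goes into the error term although it cannot contribute to the arm differences. The standard error then overstates the real uncertainty, and the test rejects less often than its nominal level. With a fixed sample of 31 units, adjustment is one of the few ways to gain precision. Arm-only summaries have a similar drawback, because their standard deviations mix two groups that the design separated on purpose.

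**Working it through.** **Inputs from the protocol article.** Two strata (high, low); arms of 10, 10 and 11 (10 + 10 + 11 = 31); model terms arm and time; trigger effect size 0.29.

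**Assumed, because the article does not state them.** Strata of 15 and 16 units, allocated 5/5/5 and 5/5/6; two-sided 5% level; pre-post correlation 0.5; the 0.29 read as Cohen's f.

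**1. The plan's own figure.** For the time-by-arm interaction with two time points, λ = f² × N × 2/(1 − ρ) = 0.29² × 31 × 2/0.5 = 10.43 on 2 and 28 df. Power is 0.787, and the effect detectable with 80% power is f = 0.294. So 0.29 is consistent with a minimum detectable effect, but only under these assumptions. Power runs from 0.476 at ρ = 0 to 0.994 at ρ = 0.8.

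**2. What variation is left in the error term.** The time-by-arm test with two time points is a one-way ANOVA on pre-post change. A stable high/low difference in level cancels from it: with strata 1 or 2 SD apart in level but changing alike, the simulated SE ratio is 1.00 and power is 0.788, against 0.786 with adjustment. Only a stratum difference in change matters there. In a between-arm test at one time point nothing cancels, so the difference in level matters. Below, δ is the stratum difference in the analysed variable, in within-stratum SDs.

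**3. Interval width.** The within-arm sum of squares of the stratum indicator is 5×5/10 + 5×5/10 + 5×6/11 = 2.5 + 2.5 + 2.727 = 7.727. The expected unadjusted error variance, relative to the within-stratum variance, is 1 + 7.727δ²/28. Its square root is the SE ratio. Multiplying by the ratio of t quantiles on 28 and 27 df (2.048/2.052 = 0.998) gives the interval ratio. The share of variance explained is (δ²/4)/(1 + δ²/4).

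| δ | Variance explained | SE ratio | Interval ratio |
|---|---|---|---|
| 0 | 0% | 1.000 | 0.998 |
| 0.5 | 5.9% | 1.034 | 1.032 |
| 0.8 | 13.8% | 1.085 | 1.083 |
| 1.0 | 20% | 1.130 | 1.128 |

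**4. Rejection rate and power, by simulation (40,000 trials per scenario for the three-arm test).** With stratum in the model, the type I error stays near 5% and three-arm power near 0.785 throughout. Without it:

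| δ | Pairwise 5% test, true null | Three-arm F test, true null | Three-arm power |
|---|---|---|---|
| 0 | 4.9% | about 5% | 0.787 |
| 0.5 | 4.2% | 4.2% | 0.774 |
| 0.8 | 3.4% | 3.2% | 0.744 |
| 1.0 | 2.9% | 2.3% | 0.714 |

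A further run of 40,000 trials gave 4.9%, 4.5%, 3.4% and 2.9% for the pairwise column. The entry at 0.5 SD is therefore good only to a few tenths of a point.

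**5. Without blocking.** When the 15/16 split falls at random across the arms, chance imbalance adds to the true variability of the arm difference. The unadjusted SE then reflects that variability, and the same simulation with strata permuted gave rejection near 5% at every δ up to 1.0. Adjustment still narrows the interval, so what is lost is efficiency, not validity.

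**The case against.** The strongest reply is that this is one table cell in a journal article, and that adjustment for assignment strata is commonly left to the analysis plan. That would succeed if the article were silent. It is not: it names the ANOVA with its interaction, the follow-up comparison and two alternatives, and that set does not match the allocation described.

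Several other replies stand and limit the point:

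- The named tests sit under aim 2c, for staff survey variables. Resident outcomes use run charts and control charts, and template use is examined by document and thematic analysis. The article does not say how well an interview-based high/low split predicts survey scores.
- The pre-post test already removes any stable difference in level.
- The article relies on descriptive statistics for the arm comparison, and the error discussed here is conservative: it adds no bias and no false positives.

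A reader might go further in three ways that the documents do not support:

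- That the error bars are simply wrong. This needs both balance within strata, which the article does not state, and a stratum that predicts the analysed variable.
- That province should also enter the allocation and the model, given "trial sites in BC (17 units) and AB (14 units"). Nothing in the article says province is prognostic, and chance imbalance under randomisation is not an error. Two strata by two provinces by three arms gives 12 cells, averaging 31/12 = 2.6 units.
- That the question of whether a booster helps low-sustaining units is lost. Baseline sustainment is recorded for assignment, so units can still be described by it, and no stated aim poses that question as a test.

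**Conclusion.** The point holds in conditional form. Allocation uses the high/low stratum, while the named between-arm tests and the summaries do not. If arms are balanced within strata, the unadjusted tests are conservative and less precise to the extent that the stratum predicts change (for the ANOVA) or level (for any between-arm p-value by time point). If there is no blocking, only precision is lost. The loss is negligible to small for stratum differences up to 0.5 SD (about 3% in interval width and 1 point of three-arm power). It is moderate at 1.0 SD (about 13% and 7 points: 0.714 against 0.785). These differences are assumptions, as are the stratum sizes, the correlation of 0.5 and the reading of 0.29, and the article gives no figure that would choose among them. High confidence attaches to the mismatch between design and analysis, not to any particular loss.

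**What to change.** In Table 1, aim 2c, include the high/low assignment stratum as a fixed factor in every between-arm model. In the repeated-measures ANOVA this means stratum and stratum-by-time, which is the same as a stratum term in the model for pre-post change. Apply the same term to any between-arm p-value by time point. Where a rank test replaces the ANOVA, use a stratified version. Show the arm summaries within stratum as well as overall, and state whether allocation is blocked within stratum.

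The cost is one residual degree of freedom, from 28 to 27, and no new data, because the stratum is recorded at assignment. If the stratum turns out to have no effect, almost nothing is lost: simulated pairwise power for a 1 SD difference is 0.597 without the term and 0.595 with it. The allocation scheme itself need not change.
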